## Methods/design

### Study setting

We are conducting the study in a large urban, federally qualified health center (FQHC) in Los Angeles that serves approximately 20,000 patients annually. The study is taking place at the FQHC’s two largest sites. We elected to hold the study in an FQHC because of the expected influx of patients into publicly funded clinics due to expanded coverage, an increased funding and an increase in the number of clinics due to the Patient Protection and Affordable Care Act (PPACA) [57], and the greater opportunity to reach more individuals who need treatment. The clinic currently has integrated mental health services and provides treatment for anxiety and depressive disorders; however, prior to the study, the clinic did not conduct any screening or treatment for SUD. If substance misuse was identified, patients were sometimes, but not systematically, referred to specialty care.

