**Figure 2 Fig2:**
[figure not shown]
SUMMIT study design and timeline.

For the RCT, all patients are screened for drug and alcohol use by clinic staff as part of usual care; eligible consenting patients (i.e., those with risky use or worse) are referred for further eligibility screening by the research staff, and eligible patients (*N* = 400) are invited to participate in the study. After consenting and completing the baseline interview at one of the study sites, patients are randomized to the ICC or SAU study condition. We use a concealed randomization protocol so neither patient nor research staff is aware of the randomization until after the baseline interview is completed when research staff open sequentially numbered envelopes that contain the randomization assignment. Assignments were made in advance by a statistician using R software. Patients complete a follow-up interview by telephone 6 months after the baseline interview.

The design is a variation of a “hybrid type 2” study, which Curran et al. [59] describe as the “simultaneous testing of a clinical intervention and an implementation intervention/strategy.” In this case, the organizational readiness intervention is the implementation intervention/strategy and the ICC service delivery intervention is the clinical intervention. The design, which incorporates implementation outcomes such as intention to adopt EBP as well as service system and patient outcomes, follows the recommendations for implementation research outcomes suggested by Proctor et al. [58].

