##### Patient outcomes

We are examining four primary patient outcomes. Patient outcomes are: (1) *Changes in quantity and frequency of substance use*. We measure this using the Timeline Follow-Back (TFLB), a validated instrument that uses a calendar to facilitate recall of substance use over the past 30 days [75]. (2) *Consequences of substance use*. To assess consequences, we use the Shortened Inventory of Problems Alcohol and Drugs (SIP-AD), a validated instrument that assesses consequences related to substance use in the past 90 days [76]. (3) *Functioning*. We assess overall health functioning with the SF12 version 2, four-week recall [77]. We use the Patient Health Questionnaire-9 (PHQ-9) [78] to assess depressive symptoms and the generalized anxiety disorder (GAD) [79] to assess symptoms of anxiety. (4) *Satisfaction with SUD care*. We use an adapted standardized patient satisfaction survey [80] to assess patient satisfaction with SUD services at the clinic.

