##### Analysis plan

Our quantitative analysis of provider survey items and administrative data related to service system outcomes will consist of pre-post, one-way repeated measures ANOVA comparisons of survey responses between pre- and all post-intervention periods. To analyze patient-level outcomes, we use an intent-to-treat approach. We will first conduct a bivariate analysis to estimate the uncontrolled association between being in the ICC group and outcome. In addition, even though our design randomly assigns patients, we will assess any possible imbalance in covariates between ICC and SAU groups including age, gender, race/ethnicity, and education that affect the impact of the ICC intervention on the outcomes. In cases where observed imbalances are attributable to sample attrition, we will correct for potential bias due to attrition at follow-up using response weights. In addition, characteristics related to an outcome at a conservative significance level of α = 0.2 will be considered covariates in a multivariate analysis for reduction of bias if imbalanced or for efficiency gains. For the multivariate analyses, we will infer about the impact of ICC on an outcome by fitting hierarchical models using SAS Proc Mixed, R LME4, and Winbugs. These models take into account the multi-level structure of the data: two repeated measures over time (baseline and 6 months) nested within patient and patients nested within clinics. Sensitivity analyses will be conducted testing model functional forms, the covariates to be used, and the impact of influential outliers in the analyses results. For outcomes assessed only at month 6 (e.g., treatment satisfaction), we will use cross-sectional analyses (such as linear and logistic regression) to estimate the effect of ICC relative to SAU. This study was designed to estimate sufficient effect sizes that can be detected with a power of at least 80% when comparing the outcomes of patients randomly assigned to the two conditions in an end-status analysis at month 6 for a 5% significance level. For continuous outcomes, the study will be able to detect effect sizes of about 0.30–0.32 standard deviations. These are the kind of effects that can be expected for an intervention like ICC [42]. For dichotomous outcomes, we will be able to detect a difference of 13–14 percentage points under the assumption that the SAU group has a 15% rate of receiving the outcome.

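### For outcomes measured twice, the plan models baseline as a second response without naming the ICC contrast; it should specify a baseline-adjusted month-6 difference, with site as a fixed effect

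*Protocol article*

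**What the plan says.** All references are to the Protocol article.

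- **Model.** The Analysis plan for the service delivery intervention infers the ICC effect from hierarchical models whose structure is "two repeated measures over time (baseline and 6 months) nested within patient and patients nested within clinics". Cross-sectional regression is kept for outcomes assessed only at month 6, such as satisfaction.
- **Covariates.** Characteristics related to an outcome at α = 0.2 may enter the multivariate model. The baseline value of the outcome is not named among them.
- **Power.** At least 80% power is stated for "comparing the outcomes of patients randomly assigned to the two conditions in an end-status analysis at month 6 for a 5% significance level". The detectable effect for continuous outcomes is about 0.30–0.32 SD.
- **Outcome label.** Under Patient outcomes, the first outcome is "Changes in quantity and frequency of substance use". The Background states the patient hypotheses for the status 6 months after enrolment.
- **Design.** Under Study design, "eligible patients (*N* = 400) are invited to participate in the study", and after the baseline interview "patients are randomized to the ICC or SAU study condition". Study setting says that the trial runs at the health centre's "two largest sites".

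**The concern.** Baseline precedes randomisation, so it carries no treatment effect. Its value to the analysis lies in explaining variation at month 6. A model that takes both occasions as responses can use it well or badly, depending on which contrast is reported and whether the baseline means are constrained. The text fixes neither. The usual output from such a model is the arm-by-time interaction, that is, the difference between arms in mean change. The outcome label, which speaks of changes, points the same way. That contrast differs from the powered analysis and is less precise than baseline adjustment. Precision on substance use, consequences and functioning could therefore be given away, and at modest correlations power would fall below the level advertised.

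The same sentence makes clinic a level of the hierarchy, although there are only two clinics.

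**Working it through.** **Inputs.** From the document: 400 patients, 5% level, 80% power, 0.30–0.32 SD, one follow-up at 6 months, two sites. Assumed because not stated: 1:1 allocation, a two-sided test, equal SDs at the two occasions, and r from 0.2 to 0.7.

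**1. Reproducing the stated figure.** Patients per arm = 2 × ((1.960 + 0.842)/d)².
- d = 0.30: 2 × 7.85/0.0900 = 174.4, so 175 per arm (350 in all, 12.5% loss from 400).
- d = 0.32: 2 × 7.85/0.1024 = 153.3, so 154 per arm (308 in all, 23% loss).
- With all 400 analysed, the detectable effect is 2.80 × √(2/200) = 0.28 SD.

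The stated range is therefore right for an end-status test with 12.5–23% loss, a rate that the document does not give.

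**2. Variance of the ICC effect relative to the unadjusted month-6 difference.**
- Arm-by-time contrast, free baseline means: 2(1−r)
- Month-6 contrast from the same model, free baseline means: 1
- Two-occasion model with baseline means held equal: 1−r²
- Month-6 regression on arm and baseline (ANCOVA): 1−r²

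Generalised least squares at r = 0.3/0.5/0.7 gave 1.40/1.00/0.60, then 1.00 throughout, then 0.91/0.75/0.51 for each of the last two. The ratio of the first to the last is 2(1−r)/(1−r²) = 2/(1+r), which exceeds 1 for every r below 1.

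**3. Power at the stated effects.** Power = Φ(d√(n/2)/√v − 1.96), where v is the relative variance. With d = 0.30 and n = 175, d√(n/2) = 2.806. At r = 0.3, for example:
- change: 2.806/√1.40 − 1.96 = 0.41, power 66%
- ANCOVA: 2.806/√0.91 − 1.96 = 0.98, power 84%

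The pair d = 0.32, n = 154 gives the same powers to within rounding.

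| r | 2(1−r) | 1−r² | Ratio | Power, arm-by-time | Power, baseline-adjusted |
|---|---|---|---|---|---|
| 0.2 | 1.60 | 0.96 | 1.67 | 60% | 82% |
| 0.3 | 1.40 | 0.91 | 1.54 | 66% | 84% |
| 0.4 | 1.20 | 0.84 | 1.43 | 73% | 86% |
| 0.5 | 1.00 | 0.75 | 1.33 | 80% | 90% |
| 0.6 | 0.80 | 0.64 | 1.25 | 88% | 94% |
| 0.7 | 0.60 | 0.51 | 1.18 | 95% | 98% |

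Unadjusted end-status stays at 80% throughout. The effect detectable with 80% power is 0.35–0.38 SD (change) against 0.29–0.31 SD (adjusted) at r = 0.3, and 0.30–0.32 against 0.26–0.28 SD at r = 0.5.

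**4. Two clinics.** A between-clinic variance would rest on 1 degree of freedom. The chi-square limits are 5.02 and 0.00098, so the 95% interval runs from 1/5.02 = 0.2 to about 1,018 times the estimated variance, or 0.45 to 32 times the SD. In 100 simulated trials analysed both ways, the standard error of the ICC effect was 0.0985 with site fixed and 0.0985 with site random. Some random-site fits gave convergence or boundary warnings.

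**The case against.** The strongest reply is that taking baseline as a response is not itself a defect. The same model yields the month-6 difference directly: with free baseline means it has exactly the end-status variance, and with equal baseline means it matches ANCOVA. The text names no contrast and excludes neither. It allows covariates for efficiency and sensitivity analyses of the covariate set, and an article commonly leaves such details to the SAP. The arm-by-time contrast also reaches 80% power at r = 0.5 and exceeds it above that. All of this is correct and limits the point.

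What it does not remove is that the article states a method. It sends outcomes measured twice to the two-response model and reserves month-6 regression for outcomes measured once. A concrete alternative, using data already collected, is never less precise than the powered analysis and beats the arm-by-time contrast at every r below 1.

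A reader might also infer stronger things that the document does not support:
- *That the stated power is wrong.* It reproduces and is openly labelled as end-status.
- *That the ICC effect will be averaged over both occasions and so halved.* Nothing in the text suggests this; both the hypothesis and the power statement concern month 6.
- *That a fixed site term sharpens the ICC estimate, or that the three packages will disagree on it.* Patients are randomised individually, and the standard error is the same either way. Whether clinic is random is not stated outright, although nesting suggests it.

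**Conclusion.** The point holds as a recommendation to specify a better analysis, not as an error in the power figures. Under the arm-by-time reading, power at 0.30–0.32 SD runs from 60% to 95% as r goes from 0.2 to 0.7, against 82% to 98% with baseline adjustment, and it is below the stated 80% whenever r is under 0.5. How much is lost depends on r, which the document does not give, and on that contrast being the one reported. If the month-6 contrast with free means is reported instead, power equals the stated 80%, and only the gain from baseline is forgone. The site point is secondary: it concerns whether a variance can be estimated from two units, with no material effect on the ICC estimate or its standard error.

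**What to change.** For each outcome measured at both occasions:

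1. Define the ICC effect as the month-6 difference between arms, adjusted for the baseline value of that outcome. Equivalently, use a two-occasion model with baseline means constrained equal across arms.
2. Enter site as a fixed effect and remove clinic as a random level.
3. State that the 80% power at 0.30–0.32 SD is for the unadjusted comparison and is a floor for the adjusted one.

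The cost is wording in the analysis plan and one degree of freedom each for baseline and site. The baseline interview is already part of the design. Trial status puts the RCT at month 11 of 18 planned months of enrolment and data collection, so the choice can be fixed before analysis.

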### Trial status

The RCT is currently in month 11 of 18 planned months of active enrollment and data collection.

## Discussion

The present study responds to several critical gaps in health care services for people with SUD—the need for greater access to SUD treatment, the need for more evidence to support the growing emphasis on collaborative, integrated care for SUD in primary care settings, and the call for broader dissemination and adoption of evidence-based treatments for SUD in general and in medical settings in particular. To meet these diverse and complex needs, we designed a multi-level study that (1) combines well-studied implementation tools into an intervention to increase organizational readiness to adopt and sustain SUD EBPs in primary care and (2) tests the effectiveness of a service delivery intervention (ICC) on service system and patient outcomes related to SUD services.

Our hybrid type 2 design [59] allows us to support and study important organizational changes thought to be critical for the adoption and sustainability of new practices and to add what we believe is a necessary component of integrating SUD EBP into primary care—a service delivery intervention tailored to meet clinic specifications and the complex needs of patients with SUD treated in these settings. The study’s unique design takes into account the complexity of introducing new EBPs into a clinical setting, the barriers to integrating SUD EBP into primary care, and the chronic nature of SUD and the corresponding complex needs of SUD patients. We believe that our 18-month organizational readiness phase, starting with preparing the organization for SUD EBP delivery and ending with a pilot phase to ensure that the ICC intervention (i.e., service delivery system intervention) and EBP protocols fit the environment will ensure greater organizational readiness and thus greater likelihood of adoption and sustainability. We believe our multi-level approach—addressing organizational change plus SUD-specific service delivery—is necessary for adoption and sustainability of SUD EBP in primary care. The organizational readiness outcomes will allow us to assess whether our organizational readiness intervention improves provider perceptions of and intention to adopt the EBP while the service delivery intervention will help determine whether the ICC delivery system improves quality of care and patient outcomes compared to service delivery as usual.

Despite the study’s strengths, there are some limitations. One limitation is the lack of provider randomization to test the effects of ICC on provider outcomes. This was determined to be infeasible, due to potential contamination across study conditions and lack of provider and patient support for asking patients to switch providers to match their study condition. Additionally, because we are testing the combined impact of the organizational readiness intervention with the ICC intervention, we will not be able to draw conclusions about the unique contribution of either intervention on EBP implementation, sustainability, or patient outcomes. Moreover, both the organizational readiness and the ICC interventions are complex, containing multiple elements. We will be unable to tease apart the impact of particular elements of the interventions (e.g., the effect of the decision support system from the self-management support) on outcomes. Given the emphasis on examining two complex interventions simultaneously, we elected to examine them initially in one FQHC serving a diverse population in a large metropolitan area in California. It is important to note that this occurred during a time of rapid health care reform especially in California, a state that was an early adopter of Medicaid expansion. We will not know whether our study results will be applicable to other FQHCs or in other geographical locations.
